# Methods: Monitoring

## Data monitoring

### 20a Role of Data Safety and Monitoring Board (DSMB)

It is expected the trial enrolment will be complete within 3-4 months, due to high caseloads in the catchment area of each health facility. Due to the short duration of the trial (8 months, including 4 months for completion of treatment of the last enrolled child), meaningful interim analysis by a DSMB will be difficult. However, in order to have independent oversight of the safety aspects of the trial, a Trial Safety Committee (TSC) will be formed. The TSC will comprise of an independent chair, a statistician from the LSHTM, and a health official from each country (Kenya and South Sudan).

### 20b Description of any interim analyses and stopping guidelines, including who will have access to these interim results and make the final decision to terminate the trial

The TSC will review the study outcomes and adverse events at the mid-point of the trial to determine if the trial can proceed. Adverse events will include deaths and hospitalizations.

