## Participant timeline

Once the study begins, all existing patients in the health facilities assigned to the intervention will complete treatment per the standard protocol, and all new patients eligible for inclusion will begin treatment per the Combined Protocol.

Enrolment: March- June 2017

SQUEAC: June 2017

Qualitative study: June 2017

End of study: October 2017

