## Recruitment

Prior to randomization of health facilities to either the control or intervention group, community health workers will conduct a sensitization campaign across the communities that fall within the catchment area of the 12 facilities in each country. The goal of the campaign will be to meet with community leaders and encourage them to send malnourished children to the clinics for treatment. Randomization of the facilities will occur prior to the start of the trainings of the field teams, as research officers will only be trained on the protocol they are to implement. Screening to detect malnourished cases will take place after the randomization, since referral of children to the facilities cannot begin until the teams are trained and in place and ready to provide services. Community health workers will conduct screenings in an equivalent manner across the catchment areas of both arms of the study. All malnourished children (i.e. MUAC <125mm) will receive a referral slip and their caretaker will receive instructions on how to access treatment. For any medically complicated cases requiring immediate treatment, IRC/ACF will provide transportation to the nearest stabilization center.

Patients who present to health facilities on their own will also be screened for inclusion. Weight and height measurements will be taken at the health facility only (in addition ot MUAC measurements), per national and international guidelines. All patients eligible to participate in the study based on the inclusion and exclusion criteria will be invited to enrol in the study.

In Nairobi, Kenya in 2015 the average monthly enrolment at each health facility of children classified with acute malnutrition according to the primary study definition of <125mm MUAC is 30. It is expected it will take four months to reach the sample size in Nairobi.

In Aweil East, South Sudan in 2015 the average monthly enrolment at each health facility of children classified with acute malnutrition according to the study definition of <125mm MUAC is 80. It is expected it will take two months to reach the sample size in Aweil East.

Using the above averages, enrolment is expected to take a minimum of four months, with an additional 4 months for completion of treatment of the last enrolled child. Therefore the study is expected to take 8 months.

Enrolment will occur over a period when malnutrition tends to be at its highest.

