## Harms

**Plans for collecting, assessing, reporting, and managing solicited and spontaneously reported adverse events and other unintended effects of trial interventions or trial conduct**

The RUTF used in this study will be stored according to USAID guidelines outlined in appendix B. When stored at 26.7°C (80°F), RUTF has a shelf life of 24 months. The expiry date of RUTF used in this trial will be monitored by the ACF and IRC drug management teams in each location. RUTF in South Sudan will be stored in ACF warehouses currently used to store RUTF for existing programs in Aweil East, and RUTF in Kenya will be stored in IRC warehouses in Nairobi currently used to store RUTF prior to shipment to field programs.

The trial safety committee will review all cases of children who were hospitalized or who died at the trial mid-point to determine if these cases were study-related. Any cases deemed to be study-related will be reported to the PI and co-investigators, who will discuss with the IRB at LSHTM and in-country.

During the enrolment process each participant’s caretaker will be provided with the contact information for a point person who will be responsible for fielding complaints and concerns. The point person will not be the research coordinator or the research officer based at the health facility, but a third party representative who is not a part of the research team and can field concerns neutrally and without the participant fearing a loss of access to treatment. The point person will bring concerns to the research coordinator maintaining the anonymity of the study participant(s). The research coordinator will raise the issues with the PI and study team in order to find a resolution.

Additionally, the Community Health Workers (CHWs) employed by the project will organize monthly focus group discussions at the community level to understand perceptions of the program and solicit advice and feedback.

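### The only planned independent safety review falls at about month 4 of 8, when enrolment is due to be over, so it can hardly limit enrolment into a harmful arm

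*Protocol*

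**What the plan says.** Section 20a of the protocol explains why there is no data safety and monitoring board and sets up a Trial Safety Committee as the independent oversight of safety. Section 20b states what the committee does: "The TSC will review the study outcomes and adverse events at the mid-point of the trial to determine if the trial can proceed". It counts deaths and hospitalisations as the adverse events. The Harms section (21) repeats the timing: "The trial safety committee will review all cases of children who were hospitalized or who died at the trial mid-point". The committee then judges whether each case is related to the study. Related cases go to the principal investigator and co-investigators, who take them up with the ethics committees. No other committee meeting is described.

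The mid-point is not given as a month or a date for this review. The timeline is spread over three places:

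- Section 20a: "It is expected the trial enrolment will be complete within 3-4 months".
- Recruitment (section 15): "enrolment is expected to take a minimum of four months, with an additional 4 months for completion of treatment of the last enrolled child", followed by "Therefore the study is expected to take 8 months". For South Sudan: "It is expected it will take two months to reach the sample size in Aweil East".
- Participant timeline (section 13): "Enrolment: March- June 2017" and "End of study: October 2017".

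**The concern.** A review that decides whether a trial may continue protects children in two ways. It can stop further children from entering a harmful arm, and it can change what happens to those already in treatment. The first works only if the review comes while a useful share of children is still to be enrolled. Here accrual is fast and the review is set at half of the total study time, not at a stage of enrolment. If the mid-point and the end of enrolment coincide, an excess of deaths or admissions in one arm would be examined independently only after nearly all children had been allocated to treatment.

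There is a second gap. As written, the committee's judgement on relatedness, and the only stated route from an event to the ethics committees, both hang on this one meeting. Nothing is planned for the committee between the mid-point and the last child's exit.

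**Working it through.** **Step 1: when is the mid-point?** Section 15 gives 4 months of enrolment plus 4 months of treatment for the last child: 4 + 4 = 8 months, which reproduces the stated duration. Half is month 4. By the calendar in section 13, the mid-point of March to October 2017 falls between 16 June (1 March to 1 October) and 8 July (16 March to 31 October), depending on the days chosen. The protocol also uses the term elsewhere: section 18a sets the coverage survey at the trial mid-point, under a heading that places it after enrolment has finished. All three point to the end of enrolment.

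**Step 2: how many are enrolled by then?** Inputs: 150 children per cluster (section 14); 12 facilities per country (section 8), so 1,800 per country and 3,600 in all; 30 children per facility per month in Nairobi and 80 in Aweil East (section 15).

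Time to target: 150/80 = 1.9 months in South Sudan, in line with the stated two months; 150/30 = 5 months in Nairobi, where the protocol states four (4 × 30 = 120 per facility).

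Enrolled by month m = 12 × min(30m, 150) + 12 × min(80m, 150):

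| Month | Kenya | South Sudan | Total | Share of 3,600 |
|---|---|---|---|---|
| 1 | 360 | 960 | 1,320 | 37% |
| 1.5 | 540 | 1,440 | 1,980 | 55% |
| 2 | 720 | 1,800 | 2,520 | 70% |
| 3.5 | 1,260 | 1,800 | 3,060 | 85% |
| 4 | 1,440 | 1,800 | 3,240 | 90% |

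On the monthly rates, 360 Kenyan children (10% of 3,600) are still to enrol at month 4. On the stated four months for Nairobi, none are. If Nairobi takes 5 months, the study lasts 5 + 4 = 9 months, the mid-point is month 4.5, and (12 × 135 + 1,800)/3,600 = 3,420/3,600 = 95% are enrolled. The earliest calendar mid-point, 16 June, is about month 3.5 after a 1 March start and gives 85%. South Sudan is fully enrolled on every reading.

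**Step 3: who could still benefit at month 4?** The protocol forecasts no length of stay, so this rests on an assumed fixed stay L, the same in both arms. In treatment at month 4 = enrolled by month 4 minus enrolled by month (4 − L), with weeks converted at 52/12 per month:

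| Assumed stay | Kenya | South Sudan | Total | Share of 3,600 |
|---|---|---|---|---|
| 6 weeks | 498 | 0 | 498 | 14% |
| 8 weeks | 665 | 0 | 665 | 18% |
| 12 weeks | 997 | 618 | 1,615 | 45% |
| 16 weeks | 1,329 | 1,505 | 2,834 | 79% |

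Sixteen weeks is the limit in the Combined Protocol only. South Sudan controls have 2 months in the outpatient therapeutic program and 3 months in supplementary feeding, with referral from one to the other, so the last row is not a ceiling for them.

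**The case against.** The strongest case for the plan has four parts.

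*Enrolment is not completed exposure.* A reader might infer that a month-4 review cannot protect anyone. The documents do not support that: the last child enrolled has up to four months of treatment ahead, and under the assumed stays 14% to 79% of the target sample is still in treatment. Nor do they support saying that no enrolment at all would be left, because at 30 per facility per month 360 Kenyan children would remain. This part stands and limits the finding to enrolment.

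*Other safeguards exist.* A reader might also infer that a death in week 2 goes unnoticed until month 4. The text does not say so. The protocol commits to good clinical practice and local regulations. Children with complications or poor response are referred (sections 11a, 11b and 11d), the principal investigator reviews the data weekly (section 19), and caretakers have a neutral contact (section 21). But these act on single children or sit with the study team of an unblinded trial. None is an independent comparison of the arms.

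*The trial is short.* Section 20a argues that its brevity makes a useful interim analysis difficult. That is a fair reason for no formal efficacy look. It does not explain why individual deaths and admissions should reach the committee only once, at the end of enrolment.

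*An early look would be thin.* This also stands. The protocol gives no expected death or hospitalisation rate, so no one can show from it that an early review would detect an excess. Recovery would be almost unobservable, since cure in the combined arm needs a stay of at least three weeks.

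**Conclusion.** The finding holds as a matter of timing. One independent safety review is planned, at a mid-point that the protocol does not define for this purpose but that works out to about month 4. Enrolment is due to be complete then: 100% on the stated enrolment times, 90% on the stated monthly rates. South Sudan, half of the sample, has been closed for about two months. The go or no-go decision can therefore hardly limit enrolment into a harmful arm, and in South Sudan cannot limit it at all. It can still matter for children in treatment; with stays of 6 to 8 weeks these are all in Kenya. Events after the mid-point have no planned committee review.

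This rests on month 4 being the intended mid-point, which is a well-supported inference and not a stated date, and on enrolment running at the 2015 rates. The in-treatment shares rest on assumed stays and only show the range.

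**What to change.** In sections 20b and 21:

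1. Define the first committee review by number enrolled in each country, so that it falls before that country closes: before about month 1.9 in South Sudan. As an illustration, half of each country's 1,800 is reached at 75/80 = 0.94 month in South Sudan and 75/30 = 2.5 months in Kenya.
2. Limit this early look to deaths and hospitalisations by arm, without recovery outcomes. It then adds no further look at the primary outcome.
3. Send each death and hospitalisation to the committee as it occurs, until the last child exits. Given how few events an early meeting may have, this is the more valuable half of the change.
4. Keep the mid-point meeting as a second look, and state its date or trigger.

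The cost is some extra committee contacts and the forwarding of data that are already collected and reviewed weekly. The early look would be sparse: with even entry over 0.94 month (about 4 weeks), mean follow-up in South Sudan would be about 2 weeks. A later trigger gives more follow-up but leaves fewer children to spare; at month 1.5, 1,440 of 1,800 there (80%) are already enrolled.

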## Harms

**Plans for collecting, assessing, reporting, and managing solicited and spontaneously reported adverse events and other unintended effects of trial interventions or trial conduct**

The RUTF used in this study will be stored according to USAID guidelines outlined in appendix B. When stored at 26.7°C (80°F), RUTF has a shelf life of 24 months. The expiry date of RUTF used in this trial will be monitored by the ACF and IRC drug management teams in each location. RUTF in South Sudan will be stored in ACF warehouses currently used to store RUTF for existing programs in Aweil East, and RUTF in Kenya will be stored in IRC warehouses in Nairobi currently used to store RUTF prior to shipment to field programs.

The trial safety committee will review all cases of children who were hospitalized or who died at the trial mid-point to determine if these cases were study-related. Any cases deemed to be study-related will be reported to the PI and co-investigators, who will discuss with the IRB at LSHTM and in-country.

During the enrolment process each participant’s caretaker will be provided with the contact information for a point person who will be responsible for fielding complaints and concerns. The point person will not be the research coordinator or the research officer based at the health facility, but a third party representative who is not a part of the research team and can field concerns neutrally and without the participant fearing a loss of access to treatment. The point person will bring concerns to the research coordinator maintaining the anonymity of the study participant(s). The research coordinator will raise the issues with the PI and study team in order to find a resolution.

Additionally, the Community Health Workers (CHWs) employed by the project will organize monthly focus group discussions at the community level to understand perceptions of the program and solicit advice and feedback.

# Ethics and dissemination

## Research ethics approval

This study protocol has been approved by the following ethical review committees:

1. Kenya Medical Research Institute (KEMRI), Nairobi, Kenya
2. Ministry of Health Ethical Committee, Juba, South Sudan
3. LSHTM, London, United Kingdom

## Protocol amendments

Any important protocol modification (including but not limited to any changes to the treatment or those eligible for it, and/or how data will be collected, managed and reported) will be described in an amendment to this document and re-submitted to the three REC/IRB’s listed in section 24.

## Consent or assent

As this is a cluster randomized trial, consent will be obtained at the health facility level from local health authorities as well as from individual participants.

Health facility-level consent will be discussed between the research coordinator, community leaders and the MoH in each county. Community leaders and local health authorities designated by the MoH will receive a ‘health facility information sheet,’ and will be asked for their consent after they have had an opportunity to review the information and discuss any questions with the research coordinator.

When a caretaker arrives to any health facility included in the ComPAS trial seeking treatment for their malnourished child (either with a referral slip or not), they will first be seen by a community health worker to confirm that they are eligible to receive treatment (i.e., they have a MUAC <125mm, and/or a WHZ <-2 z-scores, and/or oedema). Once their eligibility for treatment is confirmed, they will be seen by the health worker responsible for their care. The health worker will describe the aims of the study as detailed in the ‘participant information sheet,’ ensuring that the caretaker feels comfortable and understands the information. They will be informed that a study is taking place at this health facility and will be given information about what their participation would entail, including how their information will be used, but that they are not obligated to participate. The participant information sheet provides details of the treatments provided in the study. Treatment will be available for all malnourished children who meet the national standards (per the eligibility criteria described above and in the interventions section of the study protocol) regardless of whether they choose to participate in the study or not. If a caretaker has chosen not to participate in the study, they will be assured that their child can still receive the treatment offered by that health facility, and that their information will not be included in the analysis.

## Confidentiality

Personal information (child’s name, address and age and a unique ID) will be included in the database housed at field level until treatment is complete and all data cross-checked. Name, address and age will be removed from the database before analysis, with only the unique ID remaining. Only co-investigators (those listed as part of the research team) will have access to the database.

No personal information will be shared for research purposes. The list of personal information will be used solely to track children for counselling to ensure completion of treatment, and to ensure data quality. After the close of the study and before final analysis all personal information will be deleted.

## Declaration of interests

No conflict of interest is declared by the principal investigator.

## Access to data

The final trial dataset will be made available to the institutions involved in implementing, funding or supporting the research:

- MOH, Kenya
- KEMRI, Kenya
- MOH, South Sudan
- Drug and Food Control Authority, South Sudan
- National Bureau of Statistics, South Sudan
- ComPAS expert committee
- IRC
- ACF-USA
- ACF-UK
- LSHTM
- USAID/OFDA
- CIFF
- WFP
- UNICEF
- WHO

## Dissemination policy

### 28a Plans for investigators and sponsor to communicate trial results to participants, healthcare professionals, the public, and other relevant groups

The final trial results will be written into a final report and shared with the institutions described in section 27. The interpretation of results, implications and next steps will be discussed with the MoH in each country, the expert committee and the consultative committee before dissemination or publication at either national or international levels.

A presentation will be made at the Nutrition Information Technical Working Group and the Emergency Nutrition Advisory Committee in Nairobi, Kenya and at the MoH and Nutrition Cluster in Juba, South Sudan to review the finalized results with key national stakeholders and discuss next steps for dissemination and publication.

Results will also be shared with key global nutrition committees and working groups, including the Global Nutrition Cluster (GNC), the Emergency Nutrition Network (ENN) and the Nutrition Forum, among others.

An article for publication in a peer-reviewed journal will be prepared summarizing the key outcomes of the trial and the implications for nutrition program policy. A separate article will be prepared summarizing the key outcomes of the cost-effectiveness analysis.

A workshop will be organized within one year of the trial end date to present the finalized analyses and discuss the policy implications. The workshop will be open to all key stakeholders (Non Governmental Organizations(NGO), donors, the United Nations (UN), Ministries of Health, universities) involved in the ComPAS study.

### 28b Authorship eligibility guidelines

International Committee of Medical Journal Editors (ICMJE) guidelines for authorship eligibility will be followed. No professional writers will be used.

Per the ICMJE, authorship will be based on the following four criteria:

- Substantial contributions to the conception or design of the work; or the acquisition, analysis, or interpretation of data for the work; AND
- Drafting the work or revising it critically for important intellectual content; AND
- Final approval of the version to be published; AND
- Agreement to be accountable for all aspects of the work in ensuring that questions related to the accuracy or integrity of any part of the work are appropriately investigated and resolved.

### 28c Plans for granting public access to the full protocol, participant-level dataset, and statistical code

The study protocol and statistical code will be made available to the public. The participant-level database will only be shared with the institutions listed in section 29.

